**Fig 3 pone.0328211.g003:**
[figure not shown]
Open cot – Radiant warmer.

### EEG tool, data collection and processing

EEG is an electrophysiological imaging tool commonly used in medicine and research. The electroencephalogram measures changes in electrical dynamics resulting from the formation of electrical dipoles during nerve stimulation. The EEG signal consists of several brain waves that reflect electrical activity in the brain, based on electrode placement and function in adjacent brain areas. EEG-based changes in response to interventions have become a popular method for investigating brain function in patients with various brain and mental health disorders (e.g., [73]), as well as in healthy individuals (e.g., [74]). Moreover, EEG techniques have been successfully applied for many years in both premature newborns and full-term infants (e.g., [75–76]).

In our study, we decided to use the **nëo™** EEG monitoring unit by ANT, a specialized tool designed for both routine and advanced neonatal care in NICUs. Eight high-precision channels found on a clinical-grade infant-sized cap are applied on our participants, connected to a research-grade amplifier with an input impedance exceeding 1 GΩ and advanced noise reduction. We chose this EEG system as it supports neuroprotective intervention screening, offering a maximum sampling rate of 512 Hz and 24-bit resolution.

For the raw EEG data preprocessing part, we have configured a pipeline specialized for the premature infants (as shown in supplementary S1 Data, and presented in [77–79]), while for the processing part we followed and adapted to our protocol a specialized for the premature infants’ population quantitative EEG (qEEG) software developed for neonatal EEG by O’Toole & Boylan [80]. This software has been selected as our preferred EEG processing tool due to its highly informative, detailed, and objective output. Coupled with our preprocessing pipeline, this tool proved to be particularly advantageous for our research, as it allowed for the analysis of various EEG features such as spectral power, coherence, and connectivity among EEG channels, taking into consideration the intervention’s musical conditions and their short delivery profile.

We aimed for this comprehensive EEG setup to enhance our ability to interpret the complex EEG data from our participants in greater detail, as these infants, compared to term infants, toddlers, and adults, exhibit unstable physiological and electroencephalographic states – such as signal continuity/discontinuity [81,82] and increased artifact generation [83–84] – making it significantly more challenging to identify patterns and trends in the EEG data collected following our musical protocol.

### Participants

Premature newborns who meet the inclusion criteria outlined below are eligible for participation in our exploratory study. These criteria have been carefully selected to ensure that the infants included have the appropriate health profile for safe participation and that the study results will be as accurate and relevant as possible. More specifically, to be eligible, newborns must have been born at 32 weeks of gestation or less and weigh at least 1000 grams, while not exceeding 38 weeks of postmenstrual age (PMA) during the intervention and measurement period. It is essential that potential participants do not have auditory insufficiency in the 8th cranial nerve or excessive pathology in the brainstem, while they must also have negative bilateral ‘transient evoked otoacoustic emissions’ – both verified during the postnatal screening by the in-house audiologist.

The eligible participants must also be in stable health, with no imminent risk of death, and must not be sedated or require sedative drug administration during the study, since this will introduce confounding factors related to brain activity that could subsequently alter the study’s findings. Any congenital, genetic, or chromosomal abnormalities, neonatal sepsis, or nuclear jaundice will also lead to exclusion, as these conditions could potentially influence brain function and interfere with the study’s results. Additionally, the participants must not be exposed to maternal use of illicit drugs during pregnancy, while mechanical ventilation used for their life support – that generates excessive noise, such as high-frequency oscillatory ventilation – is another exclusion criterion.

Should a participant be diagnosed with a disease or dysfunction during the course of the study, they will be automatically excluded if the medical staff recommends their removal for health reasons. Additionally, the study protocol mandates that no external musical stimulation, including singing, be allowed for the enrolled participants during the admission period. Non-compliance with this guideline will result in the exclusion of the neonate from the study to maintain the integrity of the experimental conditions and data collection process.

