## Methods

### Study design

Between 06.2023 and 12.2025, all premature newborns who meet the specific inclusion criteria (detailed below) in the NICU of the ‘Panagiotis and Aglaia Kyriakou’ Children’s Hospital in Greece will be screened, and those who qualify will be invited to participate in this exploratory study. During their stay in the NICU, this group of premature infants will be exposed to a structured live singing intervention – including varying investigative conditions of silence and singing – for four days within one week. In terms of measurements, electroencephalography (EEG) will be used to record the newborns’ brain activity throughout their participation in the exploratory study, while video data will be also recorded, forming an auxiliary part to the EEG data collection process. Blinding of the intervention is difficult to implement in this research context due to the direct involvement of parents and facilitators in delivering the singing intervention, which makes it challenging to conceal the nature of the intervention from those administering or receiving it. Based on all the above, the schedule of enrollment, intervention and assessment can be seen in Fig 1 while a flowchart of the study design is shown in Fig 2.

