We decided to include the two different musical stimuli – the note A and the lullaby song – in order to differentiate between the effects of a simple, consistent auditory stimulus and a more complex, emotionally rich stimulus. Note A represents a controlled and repetitive sound, allowing us to observe basic auditory processing in the infants’ brains. The lullaby, on the other hand, is a complex acoustic stimulus designed to mimic a natural caregiving experience, thereby engaging additional cognitive and affective neural processes. By comparing these two types of stimuli, we aim to understand how different levels of auditory complexity impact neurodevelopmental outcomes.

We furthermore decided to introduce the periods of silence before and after each singing stage to facilitate a return to the baseline of brain activity between the two singing stages, as well as to reduce the potential impact of any residual neural activity from the previous stage. This approach will enable us to achieve a more accurate assessment of the effects of each individual singing stage, and it will also allow for a clearer comparison of the developmental trajectory of the EEG baselines. By incorporating these controlled intervals of silence, we aim to isolate the neurophysiological effects specific to each condition, thus providing a more precise understanding of how the infants’ brain activity evolves over the course of the intervention conditions as well as sessions.

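### The hearing criterion asks for negative otoacoustic emissions in both ears; read literally this is the wrong way round, and the required screening result should be stated plainly

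*Protocol article*

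**What the plan says.** The hearing requirements stand in one sentence of the Participants section of the protocol article. Its first part reads "It is essential that potential participants do not have auditory insufficiency in the 8th cranial nerve or excessive pathology in the brainstem". Its second part adds that "they must also have negative bilateral ‘transient evoked otoacoustic emissions". Both items are "both verified during the postnatal screening by the in-house audiologist". The article does not say what counts as negative, and it gives no pass/refer or present/absent rule for either ear. Otoacoustic emissions are not mentioned anywhere else in the supplied text.

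The same section says that the criteria were chosen to keep participation safe and so "that the study results will be as accurate and relevant as possible". Under Study design, "this group of premature infants will be exposed to a structured live singing intervention". Under Intervention, the sustained note is described as "allowing us to observe basic auditory processing in the infants’ brains".

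**The concern.** The word negative is attached to the emissions themselves, not to a screen for hearing loss. As the name says, an evoked emission is something the ear gives back when stimulated. A negative emission is then an absent one, which is the result a hearing screen would refer on. The first part of the sentence asks for an intact auditory nerve and brainstem. The second part, taken at its word, asks for no peripheral response in either ear.

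This is an operative entry rule, not background text. The primary question is whether different singing voices leave different EEG footprints, which presupposes that the infant can hear them. Under Study objectives the article also offers its design as a methodological template for other groups, so the published rule may be used outside this unit.

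**Working it through.** No figure in the article depends on this criterion, so there is nothing to recompute. The check is a reading of the sentence against itself and against the rest of the article. It uses one fact that the article does not spell out: an otoacoustic emission is produced by the cochlea, so its presence is the favourable finding.

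**Step 1: who is eligible under each reading.** The criterion concerns both ears, which gives three types of infant.

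| Emissions | Literal reading (emission absent in both ears) | Likely intended reading (no hearing impairment found in either ear) |
|---|---|---|
| Present in both ears | not eligible | eligible |
| Absent in both ears | eligible | not eligible |
| Present in one ear only | not eligible | not eligible |

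No infant is eligible under both readings. The choice of reading therefore reverses the rule.

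**Step 2: does the neighbouring clause settle it?** Only in part. The requirement that "potential participants do not have auditory insufficiency in the 8th cranial nerve" shows that the authors want infants who can hear, so it points to the intended reading. It covers the nerve, and the words that follow it cover the brainstem. Neither covers the cochlea, so the emissions clause is the only cochlear criterion, and no second one would catch an infant misclassified by it.

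**Step 3: does anything else define the term?** No. Verification is assigned to the audiologist, but the result to be verified is not stated. The introduction, in its section on delivering live music in the NICU, stresses how vulnerable the inner-ear hair cells are. That fits a wish for intact cochlear function and not its opposite.

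**Step 4: how much one misclassified infant would weigh.**
- Planned sample (Table 1): 14 infants, so one is 1/14 = 7.1%.
- Preliminary data (Primary outcomes): 100 observations from 5 infants, 20 each, so one is 20/100 = 20%.

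These are shares of the data, not estimates of bias. The article has no figure from which a bias could be calculated. An infant with impaired cochlear function would be expected to blur differences between facilitators, but by how much is unknown.

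**Step 5: design quantities.** Table 1 uses effect size, alpha, power, number of measurements, correlation and the nonsphericity correction. None of them involves the hearing criterion, so the 14 infants, the 0.05 and the 0.80 stand as they are.

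**The case against.** The strongest reply is that the intent is plain. The sentence opens by ruling out auditory insufficiency and then adds a further condition, so the natural reading is a second test of intact hearing. In screening language, negative is common shorthand for nothing abnormal found, and on that reading the sentence is coherent. An audiologist working on a singing study would hardly enrol only infants who failed in both ears, and a replicating group would notice the absurdity too. The slip touches no endpoint, model or comparison.

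Most of this stands. It makes a wording error much the likeliest explanation, and it limits what can be concluded. It does not make the wording correct: the adjective still qualifies the emissions, the term is undefined, and the reader has to overrule the text to reach the intended rule.

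A reader might go further and infer that infants who cannot hear were enrolled, or that the preliminary EEG results are biased towards no response. The article supports neither. It reports no screening results. An absent emission is also not the same as deafness, and a present one does not prove hearing, so even the literal rule would not simply select deaf infants and exclude hearing ones.

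**Conclusion.** The criterion is wrong as written. Taken literally it requires no recorded cochlear response in either ear, which contradicts the purpose of its own sentence and the study's reliance on hearing. It is most likely a slip for a screen negative for hearing impairment. What is established is a fault in the published entry rule; a fault in the enrolled cohort is not.

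This rests on the ordinary meaning of an evoked emission as a cochlear response, and on the absence of any other definition in the article. If the records show that every enrolled infant passed in both ears, the matter ends with the rewording. Sample size, alpha and power are unaffected in either case.

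**What to change.** 1. Reword the criterion so that it agrees with its purpose and gives the required result for each ear, for example: transient evoked otoacoustic emissions present (pass) in both the right and the left ear at the postnatal hearing screen.
2. Confirm from the existing audiology records which rule was applied to the infants already enrolled, and state this when the results are reported.
3. If any infant did not pass in both ears, keep that infant in the main analysis, report the fact, and show the mixed-model results with and without that infant as a sensitivity analysis. Removal under a rewritten criterion is not advisable now that outcomes from five infants have been seen and published.

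The cost is one sentence in the protocol and a check of records that should already exist. No new procedure, visit or infant is needed, and the article's Protocol amendments section shows that the protocol has been revised before.

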### Power calculation and sample size

In situations where an exact effect size cannot be derived from prior research or pilot data, as in our case, using the Minimum Effect Size of Interest (MESI) [85] is advantageous for guiding sample size estimation. The MESI focuses on the smallest effect size that is considered practically or clinically significant within the specific context of a study, ensuring that the power analysis is calibrated to detect effects that are both meaningful and impactful.

More specifically, for our single-arm exploratory study, the MESI was set at a small-to-medium (conservative) effect size of 0.35. Several methodological reviews support the use of such conservative thresholds to ensure that only differences with true clinical impact are detected. For example, Althubaiti [86] outlines that when using conventional effect size benchmarks – commonly adopted in regression power analyses – the effect (f^2^ = 0.35) is selected to focus on robust differences that justify the exposure of vulnerable populations to research procedures. In addition, Kang [87] demonstrates how G*Power incorporates these standardized benchmarks into its sample size calculations, emphasizing that using such conventional values ensures that the study is powered to detect only those effects that are both statistically significant and clinically meaningful. Even though our design is based on a repeated measures ANOVA rather than regression analysis, the principle remains: a higher MESI minimizes the risk of detecting trivial effects, which is particularly important given the ethical and practical constraints in neonatal research.

Most importantly, from a clinical perspective, neonatal studies must be designed to target effects that will lead to meaningful changes in patient care. Reviews in neonatal contexts (e.g., [88]) stress that interventions in this vulnerable population should only be implemented if they can yield substantial improvements in clinical outcomes, while ethical considerations – such as minimizing exposure to potentially stressful interventions – further support the choice of a conservative MESI. Particularly, Akoglu [89] emphasizes that effect size selection should reflect the minimal clinically important difference. In result, after reviewing the relevant clinical and methodological literature and consulting with field experts involved in our research protocol, the aforementioned MESI threshold was deemed appropriate, ensuring that our power analysis is finely tuned to detect only those effects that hold substantial clinical significance, thereby safeguarding patient care by focusing on differences that are both statistically robust and practically meaningful.

With our designated MESI – as explained above – and by setting alpha at 0.05 and power at 0.80, we conducted an a priori power analysis using G*Power 3.0 for an ANOVA: Repeated measures, within factors design. This analysis incorporated our 5 repeated measurement conditions (Silence1, NoteA, Silence2, Song, Silence3) to account for the experimental structure of the study, with a correlation among repeated measures and a non-sphericity correction to reflect realistic assumptions regarding the correlations and potential sphericity violations among repeated measures.

The power analysis indicated that 14 participants would be sufficient to achieve the desired power level of 80% to detect the specified effect size, with an actual power of 83% (Table 1). We should clarify that in this case we chose G*Power 3.0 as this is more tailored to adjustments specific to repeated-measures designs, such as accounting for non-sphericity and correlations among repeated measures.

**Table 1 pone.0328211.t001:** Power analysis table.

Effect Size Specification	G*Power 3.0 – F tests – ANOVA: Repeated measures, within factors	
**Tool**	**G*Power 3.1.9.7**	
		
**Analysis:**	A priori: Compute required sample size	
**Input:**	Effect size f(V)	0.35
	α err prob	0.05
	Power (1-β err prob)	0.80
	Number of groups	1
	Number of measurements	5
	Corr among rep measures	0.5
	Nonsphericity correction ε	0.75
**Output:**	Noncentrality parameter λ	12.8625
	Critical F	2.845
	Numerator df	3.00
	Denominator df	39.00
	**Total sample size**	**14**
	Actual power	0.83

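### The planning effect of 0.35 is described in three incompatible ways; the calculation used Cohen's f = 0.35, so the stated 80% power does not extend to small-to-medium effects

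*Protocol article*

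**What the plan says.** The protocol article, under the heading on power calculation and sample size, defines the minimum effect size of interest as the smallest effect that matters practically or clinically. It then states that "the MESI was set at a small-to-medium (conservative) effect size of 0.35", without naming the scale. The support offered is a regression benchmark: "the effect (f^2^ = 0.35) is selected to focus on robust differences". The same paragraph argues that "a higher MESI minimizes the risk of detecting trivial effects". The next paragraphs report an a priori calculation made "by setting alpha at 0.05 and power at 0.80", and Table 1 gives the specification as "G*Power 3.0 – F tests – ANOVA: Repeated measures, within factors". The table enters 0.35 under the label f(V), with one group, five measurements, correlation 0.5 and nonsphericity correction 0.75. Its outputs are a noncentrality parameter of 12.8625, critical F 2.845 on 3 and 39 degrees of freedom, 14 infants and actual power 0.83.

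**The concern.** The number 0.35 means very different things as f, as f² and as f(V). The article attaches the words for a modest effect, the citation for a large regression effect and a third label in the table to the same figure. By the article's own definition, this value is the smallest effect worth finding, so its description governs how a non-significant result will be read. A reader who accepts the verbal description will believe that small-to-medium effects are covered at 80% power, and may take a null result as evidence against them. The word conservative also points the wrong way: in sample-size planning a larger assumed effect gives a smaller study. The article presents itself as a methodological template, so the description may be reused elsewhere.

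**Working it through.** **Inputs, all from Table 1:** alpha 0.05, target power 0.80, m = 5 measurements, correlation ρ = 0.5, ε = 0.75, effect 0.35, N = 14.

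**Formulas (one group, within-factors repeated-measures ANOVA, effect entered as f):**
- df1 = (m − 1)ε = 4 × 0.75 = 3
- df2 = (N − 1)(m − 1)ε = 13 × 4 × 0.75 = 39
- λ = f² × N × m × ε / (1 − ρ)
- power = probability that a noncentral F with these degrees of freedom and λ exceeds the critical F

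**Step 1: reproduce the plan's figure.** With f = 0.35, λ = 0.1225 × 14 × 5 × 0.75 / 0.5 = 0.1225 × 105 = 12.8625. Critical F is 2.845 and power is 0.827. N = 13 gives 0.792, so 14 is the minimum. All printed outputs are matched.

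**Step 2: test the f(V) label.** On that scale the correlation does not enter λ separately.
- With N − 1: λ = 0.1225 × 13 × 4 × 0.75 = 4.7775, power 39%.
- With N: λ = 0.1225 × 14 × 4 × 0.75 = 5.145, power 41%.

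Neither is the printed 12.8625, so the label is wrong and the value was used as f. This agrees with the G*Power 3.0 specification named in the table.

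**Step 3: test the cited benchmark.** f² = 0.35 means f = √0.35 = 0.592. Then λ = 0.35 × 105 = 36.75 and power with 14 infants is 99.9%; six infants would reach 80%. The value actually used, f² = 0.1225, is about a third of the one cited (0.1225 / 0.35 = 0.35).

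**Step 4: test the verbal label.** The article gives no scale for small, medium and large. Assume the conventional values for f of 0.10, 0.25 and 0.40. Then 0.35 lies above medium and nearer to large. Other Table 1 inputs held:

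| f | λ at N = 14 | Power at N = 14 | N for 80% power |
|---|---|---|---|
| 0.10 | 1.05 | 11% | 147 |
| 0.175 | 3.22 | 27% | 49 |
| 0.20 | 4.20 | 34% | 38 |
| 0.25 | 6.56 | 51% | 25 |
| 0.35 | 12.86 | 83% | 14 |
| 0.592 | 36.75 | 99.9% | 6 |

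The smallest f detectable with 80% power at N = 14 is 0.339.

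**The case against.** The strongest reply is that nothing in the calculation is wrong. The article claims 80% power for the effect it specifies, the number specified is 0.35, and every output in Table 1 follows from it. That stands: this is a fault of scale and description, not of arithmetic.

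A second reply is that the surrounding text openly aims at larger effects, speaking of robust differences and of substantial clinical significance, and that all inputs are printed, so a statistician can recover the sensitivity. This also has weight, but it confirms the inconsistency. The same number cannot be small-to-medium and also be chosen because it is high.

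A third reply defends the sentence about a higher threshold: a study sized for a larger effect is indeed less likely to detect a small one. At f = 0.10, 14 infants give 11% power, whereas 147 would give 80%. The sentence is weak reasoning, because power for moderate effects falls as well, but it is not false and it is not the source of a wrong number.

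Three stronger readings are tempting, and the document supports none of them:
- A reader might infer that confusing f with f² leaves the study underpowered. It runs the other way: at the cited f² = 0.35, power is 99.9%.
- A reader might infer from the f(V) label that true power is about 40%. The printed λ rules that out.
- A reader might infer that the trial as analysed has only 11% to 51% power for modest effects. Those figures describe the five-condition ANOVA in Table 1. The planned analysis is a mixed model with facilitator and condition, and its power is not computed here or in the article.

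**Conclusion.** The point holds as a misdescription of the planning effect. The value used is Cohen's f = 0.35 (f² = 0.1225); the verbal label, the f² = 0.35 support and the f(V) label each say something else. N = 14 and 83% power are right for f = 0.35 in the five-condition ANOVA. They do not extend to small-to-medium effects, for which power in that same calculation is 11% to 51%. That range rests on two things: the conventional benchmarks for f, which the article does not give, and the article's own ρ = 0.5 and ε = 0.75. The findings that the label, the citation and the printed λ disagree need no benchmark. The correction is worth making because the stated 80% power is the sole justification given for the sample size.

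**What to change.** In the section on power and sample size and in Table 1:
1. Name the planning value as Cohen's f = 0.35 (f² = 0.1225) in the G*Power 3.0 specification.
2. Replace the small-to-medium and conservative description with medium-to-large, and cite the scale used.
3. Delete the f² = 0.35 support, which refers to a different effect size.
4. Change the f(V) label in Table 1 to f.
5. State that the 83% power applies to f = 0.35 in the five-condition repeated-measures ANOVA, and that it is about 51% at f = 0.25.

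The cost is a few sentences and one table label. No more infants are requested, and the analysis is unchanged. The downside is that the stated sensitivity becomes less favourable. If a small-to-medium effect really was intended, rewording is not enough and the sample size would have to be recalculated: 25 infants at f = 0.25, and more below that.

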- *H1*: We hypothesize that when premature newborns are exposed to a live singing intervention provided by their mother (high fundamental frequency – biological kinship) compared to the father (low fundamental frequency – biological kinship) or an unrelated male/female music therapist, they show statistically more visible short-term positive oscillatory differentiations in their brain activity.

- *H0*: We assume that there is no interaction between the fundamental frequency and the kinship profile (mother, father, man, woman) in the infant’s reactions, and that neither the fundamental frequency nor the human profile has a primary effect.

To answer the research question and study its hypotheses, this study will utilize electroencephalography (EEG) to monitor and analyze the brain activity of NICU infants. By comparing EEG patterns across different music delivery conditions of F0 and kinship source (i.e., music facilitators), the findings are expected to provide valuable insights that can be leveraged to enhance neurodevelopmental outcomes in premature infants.

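### The 14 infants and 83% power are computed for the five-level condition factor, not for the four-level facilitator comparison in the research question and H1

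*Protocol article*

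**What the plan says.** All references are to the protocol article.

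- **Study objectives.** The primary research question asks whether the EEG response differs by which of four facilitators delivers the intervention. H1 sets out the comparison for infants "exposed to a live singing intervention provided by their mother (high fundamental frequency – biological kinship) compared to the father" or an unrelated male or female music therapist. H0 adds an interaction of fundamental frequency with kinship. None of these is a comparison between silence, NoteA and Song.
- **Power calculation and sample size.** The test family is "ANOVA: Repeated measures, within factors design", run "by setting alpha at 0.05 and power at 0.80". On the effect size, "the MESI was set at a small-to-medium (conservative) effect size of 0.35". On the repeated factor: "This analysis incorporated our 5 repeated measurement conditions (Silence1, NoteA, Silence2, Song, Silence3) to account for the experimental structure of the study". Table 1 enters 5 measurements, "Corr among rep measures 0.5" and "Nonsphericity correction ε 0.75", and reports lambda 12.8625, critical F 2.845, df 3 and 39, N = 14 and actual power 0.83. The text concludes: "The power analysis indicated that 14 participants would be sufficient to achieve the desired power level of 80" percent.
- **Outcomes and statistical analysis.** The primary outcome, delta spectral power, is analysed in a mixed model with condition and facilitator as fixed effects and infant as random. Pairwise differences are then tested by LSD, with the added Type I error risk accepted openly.

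**The concern.** The number of measurements in Table 1 is the number of blocks within one session. The factor in the research question and in H1 has four levels, one per session. The calculation that fixes the sample size therefore concerns a factor that the primary hypothesis does not test, and no calculation is given for the factor that it does test.

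The sentence concluding that 14 infants suffice is not limited to the condition effect. The preliminary report leads with the facilitator effect (F(3,88) = 3.627, p = 0.016) and the mother-versus-other comparisons, so a reader may well attach the 83% to those tests. A null facilitator result at 14 infants could then be taken as adequately powered when the document gives no basis for that.

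**Working it through.** **Inputs (sample size section and Table 1).** f = 0.35, alpha = 0.05, rho = 0.5, epsilon = 0.75, N = 14, one group, m = 5 measurements. Table 1 labels the effect f(V), but its lambda shows that 0.35 was used as Cohen's f together with rho.

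**Formulas.** lambda = f² × N × m × epsilon / (1 − rho); df1 = (m − 1) × epsilon; df2 = (N − 1) × (m − 1) × epsilon; power = the probability that a noncentral F(df1, df2, lambda) exceeds the 5% critical value.

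**1. The plan's own figure, m = 5.**
- lambda = 0.1225 × 14 × 5 × 0.75 / 0.5 = 12.8625
- df = 4 × 0.75 = 3 and 13 × 3 = 39; critical F = 2.845
- power = 0.827. With 13 infants it is 0.792, so 14 is the smallest N that reaches 80%.

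Table 1 reproduces exactly. A numerator df of 3 might suggest a four-level factor without correction, but that would give lambda = 0.1225 × 14 × 4 × 1 / 0.5 = 13.72 and power 0.853, which are not the printed values.

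**2. Only m changed, to 4 facilitators.**
- lambda = 0.1225 × 14 × 4 × 0.75 / 0.5 = 10.29
- df = 3 × 0.75 = 2.25 and 13 × 2.25 = 29.25; critical F = 3.202
- power = 0.764. With 15 infants it is 0.798 and with 16 it is 0.828. At N = 14 the effect detectable with 80% power is f = 0.365.

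**3. Sensitivity of the m = 4 figure at N = 14.** The document gives no rho or epsilon for facilitators, so these values are assumptions.

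| Input varied | Power |
|---|---|
| epsilon 0.5 / 0.75 / 1 (rho 0.5) | 0.63 / 0.76 / 0.85 |
| rho 0.3 / 0.5 / 0.7 (epsilon 0.75) | 0.61 / 0.76 / 0.94 |

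Power reaches 80% at epsilon of about 0.84, or at rho of about 0.54.

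**4. Averaging over the five blocks.** Suppose f = 0.35 is defined per observation, the between-session correlation is 0.5, and the five blocks within a session correlate at w (an assumption; not in the document). The variance of a session mean is (1 + 4w)/5, so the divisor 1 − rho = 0.5 becomes (1 + 4w)/5 − 0.5.

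| w | Divisor | lambda = 5.145 / divisor | Power |
|---|---|---|---|
| 1.0 | 0.50 | 10.29 | 0.76 |
| 0.9 | 0.42 | 12.25 | 0.84 |
| 0.8 | 0.34 | 15.13 | 0.91 |
| 0.7 | 0.26 | 19.79 | 0.97 |

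If f is defined on session means instead, the 0.76 of step 2 applies.

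**5. H1 contrasts.** Assume that only the mother differs, by d standard deviations. The standard deviation of the four means is then d × √3 / 4, so f = 0.35 gives d = 0.35 × 4 / √3 = 0.81. With rho = 0.5 the SD of a paired difference is √(2 × 0.5) = 1, so the noncentrality is 0.808 × √14 = 3.02. A paired t test on 13 df at unadjusted two-sided 0.05 has power 0.798, about 80%.

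**The case against.** The strongest reply is that 76% is not the power of the planned test. The mixed model uses every block: in the five-infant run each infant gave 20 observations, and facilitator was tested on 88 denominator df. If f is per observation, step 4 puts power above 80% at each of the within-session correlations tried from 0.7 to 0.9. That stands, and it is why 76% can be given only as a like-for-like value. It does not rescue the stated 83%, which does not use that structure either.

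A reader might infer that the trial is underpowered for H1. The documents do not support this: the range in step 3 straddles 80%, both inputs are carried over from the condition factor, and each unadjusted mother-versus-other contrast sits at about 80% in the scenario of step 5. A reader might also want those contrasts at alpha/3, where the same calculation gives 62%. However, the planned post-hoc test is unadjusted LSD, so that figure belongs to an adjustment that the plan does not make.

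Nor is this an arithmetic error, since every entry in the Table 1 output reproduces. It is also fair to say that the study is called exploratory, that condition is a planned fixed effect, and that the text names the five conditions openly. These points lower the severity. They do not remove the mismatch, because the protocol chose to justify a fixed N by an a priori power and then tied that power to a factor outside its hypothesis.

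**Conclusion.** The point holds as a mismatch between the power calculation and the hypothesis, and it should be fixed. The 83% is right for the five-level condition main effect and says nothing about the four-level facilitator effect in the research question and H1.

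Under the Table 1 inputs with four measurements, power at 14 infants is 76%, about 4 points below target. That rests on carrying f = 0.35, rho = 0.5 and epsilon = 0.75 over to facilitators and on one value per session. Other plausible inputs move it to either side of 80%. The finding is that the facilitator power is unstated, not that it is shown to be inadequate.

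**What to change.** In the sample size section and Table 1, with N unchanged:

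1. Say that the 83% applies to the condition main effect only.
2. State the power at N = 14 for the facilitator effect and for the mother-versus-other contrasts.
3. Give the assumptions behind those figures: whether f is per observation or per session mean, the between-session correlation, epsilon, and the within-session correlation.
4. Give 76% (detectable f = 0.365 at 80%) as the like-for-like value under the Table 1 inputs, and about 80% for each unadjusted LSD mother-versus-other contrast if only the mother differs. Give contrast power at a reduced alpha only if a multiplicity adjustment is adopted.

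The cost is a few sentences and some extra rows in Table 1. Design, sample size and analysis stay as they are. The like-for-like power statement becomes less favourable than the one now printed.
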